### Sample size estimation

G *Power (v. 3.1) was used to estimate the sample size needed to test hypotheses 1, 2, 3 and 5. A mixed model using treatment as a between-subjects factor (MBHC, MBHC-VR, and WL) and time as a within-subjects factor (pre, inter, post, and follow-up) will be tested. Interaction effect was powered. The sample size was estimated taking as a reference a small difference in perceived stress between MBHC with vs without VR-assisted meditation in university students [5]. With an alpha criterion of .05 and a small effect size (Cohen’s d^2^ = .08), to achieve a minimum of 80% power, a minimum sample size of 174 participants will be needed. Assuming an attrition rate, based on complete dropout of approximately 20% [5], the final sample needed will include at least 210 university students (i.e., 70 participants in each of three groups).

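### The enrolment target of 210 does not keep the required 174 participants after the plan's own 20% dropout

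*Protocol article*

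**What the plan says.** All the figures are in the Sample size estimation section of the protocol article. The calculation was done in G*Power for a mixed model with "treatment as a between-subjects factor (MBHC, MBHC-VR, and WL") and four occasions as the within-subjects factor. The section adds: "Interaction effect was powered". The inputs are given as "With an alpha criterion of .05 and a small effect size (Cohen’s d^2^ = .08"). The result reads: "to achieve a minimum of 80% power, a minimum sample size of 174 participants will be needed".

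The allowance for loss follows directly: "Assuming an attrition rate, based on complete dropout of approximately 20% [5], the final sample needed will include at least 210 university students", which the section breaks down as 70 in each of three groups. The section on randomization fixes a 1:1:1 ratio, so equal arms are intended.

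**The concern.** An allowance for dropout exists so that the number required for the stated power is still there once the expected loss has occurred. If a fraction d is lost, the number to enrol is the required number divided by (1 - d). Multiplying by (1 + d) always gives too few, because the loss is taken from the larger enrolled number and not from the required one.

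Here the required number, the dropout rate and the target stand within two consecutive sentences, and the third does not follow from the other two. At stake is the claim of at least 80% power: if dropout runs exactly as the plan assumes, the trial ends below its own minimum.

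**Working it through.** **Inputs, all from Sample size estimation:** required number 174; complete dropout about 20%; target 210, or 70 per arm; 3 groups; 4 occasions; alpha .05; power at least 80%; test of the group-by-time interaction.

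**Step 1. How 210 arises.** 174 x 1.20 = 208.8. Rounded up to a whole number divisible by three, this is 210, or 70 per arm. The stated target is therefore reproduced by multiplication.

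**Step 2. What 20% dropout needs.** 174 / (1 - 0.20) = 217.5, so 218. With equal arms, 219, or 73 per arm. The target is 8 short of 218 and 9 short of 219.

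**Step 3. What 210 leaves.** 210 x 0.80 = 168, or 56 per arm. This is 174 - 168 = 6 below the minimum, 2 per arm. The largest loss that 210 can absorb is 1 - 174/210 = 17.1%.

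**Step 4. Power at 168.** This step needs quantities that the article does not give: the correlation rho between repeated measures, the sphericity value and the conversion of d to Cohen's f. I used the usual noncentral F for a within-between interaction, with k groups, m occasions and sphericity assumed:

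- noncentrality lambda = f^2 x N x m / (1 - rho)
- df1 = (k - 1)(m - 1) = 2 x 3 = 6
- df2 = (N - k)(m - 1), which is 513 at N = 174 and 495 at N = 168

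Two assumed settings return exactly 174 as the smallest equal-arm number with 80% power:

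- f = .10 and rho = .5: lambda = .01 x 4 / .5 x N = .08 x N
- d^2 = .08, so f = d/2 = .141 (f^2 = .02), and rho = 0: lambda = .02 x 4 / 1 x N = .08 x N

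The noncentrality is the same, so the two settings give the same power at every N:

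| Completers | lambda | Power |
|---|---|---|
| 168 (210 less 20%) | 13.44 | 78.8% |
| 171 | 13.68 | 79.6% |
| 174 (stated minimum) | 13.92 | 80.4% |

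The number falls below 80% as soon as it drops under 174 in equal arms.

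**The case against.** Four points can be made for the plan.

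- **The dropout rate is approximate and 210 is a floor.** Both are true. But 210 keeps 174 only up to 17.1% loss, and a floor should meet its purpose at the rate that the plan itself names. This softens the error and does not remove it.
- **The analysis is by intention to treat with maximum likelihood and EM imputation** (Data analysis section). Participants with partial data would still contribute, so 78.8% for completers need not be the exact power of the planned analysis. This stands as a caution on the power figure. It does not rescue the target: the allowance is explicitly for complete dropout, and imputation does not restore the information lost with those participants.
- **The 80% is attached to 174, and no separate power after dropout is stated.** This is correct, but the only purpose of going from 174 to 210 is to still have 174 after the loss.
- **The shortfall is trivial.** It is small, and the label below reflects that.

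A reader might go further and infer that 174 is wrong too, because Cohen's d^2 is not the effect-size measure that the interaction test takes, and because f = .141 with a correlation of .5 would need only 90 participants. From there it is a short step to saying that the trial was planned on a smaller difference than the one reported. The document does not support this. With f = d/2 and zero correlation, d^2 = .08 gives exactly 174. The value of .5 is the reader's own, since the article states no correlation. What is left is that the correlation, the sphericity value and the conversion are not reported, which a condensed article may leave to the full protocol.

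**Conclusion.** The target of 210 is wrong as written, and the error is minor in size. It leaves 168 participants after the assumed dropout where the plan requires 174; 218 are needed, or 219 in equal arms. This part rests only on figures in the section and on the standard inflation formula.

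The power consequence, about 78.8% against a stated minimum of 80%, is conditional. It assumes sphericity, an analysis of completers, and one of the two settings above that reproduce 174. No error is shown in the effect size or in the 174 itself.

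**What to change.** Correct the last sentence of Sample size estimation in one of two ways.

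- **Keep 210 (70 per arm)** and state that 20% complete dropout leaves 168 completers with about 79% power, under the correlation actually entered; or state that 210 allows for a loss of about 17%.
- **Restate the target as 219 (73 per arm)**, which retains 219 x 0.80 = 175.2, so at least 174.

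The first costs only wording and a slightly less favourable stated power. The second costs 9 more participants, 3 per arm.

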### Participants

Participants will be bachelor degree, masters, or doctorate students at Miguel Hernández University of Elche. Recruitment will be carried out over two academic years. Invitations to participate will be disseminated by institutional mailings, university’s official website, informative posters, and dissemination talks. Students interested in participating will, voluntarily pre-enroll by completing a brief online questionnaire on contact information, eligibility criteria, previous experience in meditation, and program expectations.

Inclusion criteria include: a) being 18 years old or older; b) enrolled in a bachelor degree, master or doctorate degree program at Miguel Hernández University of Elche; c) speak Spanish fluently; d) signing the Informed Consent form; and g) having internet access from a computer or smartphone to complete the online assessments and formal practices during the study. Furthermore, participants will be excluded if they: a) report a severe mental disorder in active phase diagnosed by a health professional (e.g., schizophrenia, bipolar disorder, substance abuse/dependence); b) are under the influence of alcohol or other drugs during sessions and/or assessments (determined by the program instructor); and c) participate in another standardized meditation program during the study period. Should any participants require psychological or psychiatric treatment during the study, they will be referred to specialized care services.

### Procedure

When students who wish to participate submit the form indicating their interest, eligible students will be interviewed by telephone to confirm compliance with the eligibility criteria and will be informed orally and in writing (via e-mail) about the research. If they decide to participate, they will be administered the on-line pre-intervention assessment one week before starting the program and once they give their informed consent. Ineligible students will not be allowed to enroll in the study.

Participants will not pay for MBHC training and will be rewarded with 1 European Credit Transfer System (ECTS) for their participation at the end of the study, when they have completed the last follow-up assessment.

### Randomization, allocation and blinding

Participants who satisfy eligibility criteria will be randomly assigned to one of the three intervention groups in a ratio of 1:1:1 using the randomize R package in R [39]. Randomization will be performed after the baseline assessment to preserve allocation concealment.

The participants will be randomly assigned to the MBHC, MBHC-VR or WL and informed by telephone one week before starting intervention or WL groups. Fig 1 summarizes the flowchart of the study.

**Fig 1 pone.0302018.g001:**
[figure not shown]
Flowchart of the study procedure. Abbreviations: MBHC: Mindfulness-Based Health Care; MBHC-VR: Mindfulness-Based Health Care with virtual reality; WL: waiting list.

To limit potential selection bias, members of the research team who are not involved in the assessments and implementation of the intervention will be responsible for the random sequence and data analysis.

### Intervention groups

#### Mindfulness-Based Health Care Program (MBHC)

The MBHC program is adapted for university students from the Mindfulness-Based Stress Reduction (MBSR) program [40]. MBSR is an 8-week evidence-based program that cultivates mindfulness of present-moment and a nonreactive, nonjudgmental attitude toward the experience. This version of the MBHC program [36] will be offered in-person and has a similar structure to the MBSR program but is focused for university students and introduces elements related to healthy habits and lifestyle. Features of MBHC that differ from MBSR will include: a) 6-weeks instead of 8-weeks of group instruction; b) weekly 1.5 hours sessions instead of 2.5–3 hours; and c) specific formal and informal practices aimed at cultivating healthy habits and lifestyle (e.g., activities of daily living such as feeding, bathing or showering and other occupations such as communication management, health management, etc. [41]; and prosocial components (e.g., kindness and compassion).

Core components of MBHC include: a) paying attention to the present moment; b) cultivating acceptance and openness to the present experience, without resistance and judgment; c) developing and strengthening prosocial qualities, such as kindness and compassion; d) enhancing deep self-inquiry by examining subjective experience of thoughts, feelings, and sensations; and e) promoting healthy habits and occupations. We will also include person-centered facilitation techniques, which include: 1) Unconditional positive regard; 2) Empathy; 3) Authenticity in interactions; 4) Client-centered focus; 5) Non-directive approach; 6) Self-actualisation; 7) Reflection and clarification; 8) Non-judgmental listening; 9) Holistic approach; and 10) Emphasis on the “Here and Now”; [42] and non-violent communication practices (Observation of the situation, Recognition of feelings, Identification of needs, Formulation of clear requests) [43] to support a conducive learning environment and facilitate communication. All sessions will include mindful movement, formal and informal meditation practices, sharing personal experiences and thoughts, and exercises to do at home. At the end of each session, participants will receive a set of pre-recorded audio files and printed material to support their daily practices. The structure of the MBHC program sessions is included in *S1 Appendix*. Additionally, as an example, the material of the first session is available on the web page of the B+D+b Occupational Research Group of the Miguel Hernández University.

MBHC and MBHC-VR programs will be conducted by two instructors, both with over 25 years of experience in Tibetan, Theravada and Zen meditation; experience in retreats of weeks and months in the West and Sri Lanka, and with more than 15 and 8 years of experience, respectively, facilitating mindfulness-based programs. The program has been previously implemented at Miguel Hernández University of Elche since 2016, involving university students.

#### Mindfulness-Based Health Care program with virtual reality (MBHC-VR)

Mindfulness practice with VR is an innovative way to use technology to enhance the meditation experience. This technique combines audio guided mindfulness practice (S1 Appendix) with immersion in a virtual environment that can have multiple benefits, including a higher rate of training adherence [5]. The content and objectives of MBHC and MBHC-VR programs are the same. The primary difference is that some practices (S1 Appendix) of each session will be done, within the in-person session and at home, using VR. The VR kit consists of Meta Quest 2 VR goggles and access to 360° mindfulness videos. To perform the VR practices at home, participants will be provided with VR glasses.

#### Waiting list control group (WL)

Participants in the WL control group will not receive any intervention during the study. However, for ethical reasons, at the end of the 3-month follow-up assessment, participants of this WL control group will be invited to participate in the MBHC program free of charge.

### Measures

At baseline (i.e., pre-training assessment), we will collect demographic information (age, sex, education level, marital status, work status and experience in meditation), qualitative questions about expectations regarding the program, and standardized self-report questionnaires assessing occupational balance (OBQ-X), anxiety (DASS-21), depression (DASS-21), stress (DASS-21; EMA), academic stress (SISCO Inventory), burnout (MBI-SS), emotional regulation (DERS; EMA), mindfulness (FFMQ-SF; EMA), self-compassion (SCS-SF; EMA), life satisfaction (SLS), psychological flexibility (AAQ-II; EMA), social desirability (M-C SDS), diet (PREDIMED), physical activity (IPAQ-SF), and sleep (ISI).

During the 6-weeks of MBHC or WL (i.e., inter-session assessment), information about perceived stress, emotional regulation, mindfulness, self-compassion, psychological flexibility, and volition will be collected daily by Ecological Momentary Assessment (EMA) [34]. To carry out the momentary measurements, we will use the Google Forms tool to send via smartphone daily requests for information, that will be sent daily once a day, between 19:00 to 20:00 PM, to the participants. The EMA assessment form will include questions in both text format and visual analog scales for response. A research team member will supervise the EMA and will serve as a contact and reference via telephone to respond to questions and resolve any technical difficulties.

At immediately post-MBHC or WL, we will collect self-report responses using the same assessment tools used in the baseline assessment. At 18 weeks after the baseline assessment (i.e., 3-months post-MBHC or WL follow-up assessment) the same self-report set of questionnaires (minus social desirability and mental imagery) will be administered.

### Quantitative assessment

Information about demographics, health issues, and previous meditation experience will be collected at baseline. Table 1 shows all the measures that will be used in each assessment timepoint.

**Table 1 pone.0302018.t001:** Summary of the quantitative data collection for the research.

Outcome Measures	Pre-intervention	Inter-session^a^	Post-intervention	3-month follow-up	Measurement Method
**Main outcome**					
Occupational Balance	X		X	X	OBQ-E
Anxiety	X		X	X	DASS-21
Depression	X		X	X	DASS-21
Stress	X	X	X	X	DASS-21; EMA
Academic stress	X		X	X	SISCO Inventory
Burnout	X		X	X	MBI-SS
**Secondary outcome**					
Emotional dysregulation	X	X	X	X	DERS; EMA
Mindfulness	X	X	X	X	FFMQ-SF; EMA
Self-compassion	X	X	X	X	SCS-SF; EMA
Life satisfaction	X		X	X	SLS
Psychological flexibility	X	X	X	X	AAQ-II; EMA
Social desirability	X		X		M-C SDS
Adherence to the Mediterranean Diet	X		X	X	PREDIMED
Physical activity	X		X	X	IPAQ-SF
Sleep	X		X	X	ISI
Mental representations	X		X		Psi-Q
Volition		X			EMA
Adherence		X		X	EMA; ad hoc questionnaire
**Sociodemographics**					
Age (in years)	X				ad hoc questionnaire
Sex	X				ad hoc questionnaire
Education level	X				ad hoc questionnaire
Marital status	X				ad hoc questionnaire
Work status	X				ad hoc questionnaire
Experience in mindfulness	X				ad hoc questionnaire

Abbreviations: OBQ-E Occupational Balance Questionnaire; DASS-21, Anxiety, depression and stress scale; MBI-SS, Maslach Burnout Inventory-Student Survey Questionnaire; DERS, Emotional Regulation Difficulties Scale; FFMQ-SF, The Five Facets of Mindfulness Questionnaire short FORM; SCS-SF, Self-Compassion Scale short form; SLS, Life Satisfaction Scale; AAQ-II, Acceptance and Action Questionnaire II; M-C SDS, Marlowe-Crowne Social Desirability Scale short form; Physical Activity Questionnaire short form (IPAQ-SF); Insomnia Severity Index (ISI); Plymouth Sensory Imagery Questionnaire (Psi-Q). ^a^ Inter-session measured with the Ecological Momentary Assessment (EMA).

*Main outcomes*. *Occupational Balance Questionnaire* (OBQ) [44] is a 13-item tool scored on a 6-point Likert-type response scale, ranging from 0 (strongly disagree) to 5 (strongly agree), with a total score ranging from 0 to 65, where a higher score indicates greater OB. The internal consistency of this instrument is 0.87.

*Depression*, *Anxiety and Stress Scale* (DASS-21) [45] measure psychological distress with 7 items for each subscale: depression, anxiety and stress. Participants rate the degree to which each statement has happened to them in the past week on a scale from 0 (has not happened to me) to 3 (has happened to me a lot or most of the time). The internal consistency of this assessment tool is 0.90.

Academic stress will be measured using the *SISCO Inventory* [46] which consists of 31 items distributed into: 1 filter item (yes-no), 1 item on a Likert-type scale from 1 (a little) to 5 (a lot), 8 items on a Likert-type scale from 1 (never) to 5 (always) that allow identifying stressful stimuli, 15 items on a Likert-type scale from 1 (never) to 5 (always) that allow identifying stressful stimuli divided into physical, psychological and behavioural reactions, and 6 items on a Likert-type scale from 1 (never) to 5 (always) allowing to identify the frequency of use of coping strategies. Its internal consistency is 0.90.

*Maslach Burnout Inventory-Student Survey Questionnaire* (MBI-SS) [47] contains 15 items grouped into 3 subscales: Emotional Exhaustion (5 items), Cynicism (4 items), and Academic Efficacy (6 items). These items are scored on a scale from 0 (never/never) to 6 (always/every day). High scores on burnout and cynicism and low scores on academic efficacy are indicative of burnout. The internal consistency of this instrument is 0.84.

*Secondary outcomes*. *Difficulties in Emotional Regulation Scale* (DERS) [48, 49] contains 28 items grouped into 5 subscales: emotional lack of control, life interference, lack of emotional attention, emotional confusion, and emotional rejection. These items are scored on a Likert-type scale from 1 (almost never) to 5 (almost always). Higher scores indicate greater difficulties in emotion regulation. Its internal consistency is 0.93.

*Acceptance and Action Questionnaire II* (AAQ-II) [50] measures psychological flexibility using 7 items with a 7-point Likert-type scale from 1 (never true) to 7 (always true). Scores range from 7 to 49. Higher scores indicate a tendency to act on the need to control or avoid aversive thoughts, memories, or feelings. The internal consistency of this instrument is 0.88.

*Five Facets of Mindfulness Questionnaire Short-Form* (FFMQ-SF) [51] contains 24 items that assess the five facets of mindfulness: observing, describing, acting with awareness, non-judgement of inner experience, and non-reactivity to inner experience. It is scored on a Likert-type scale from 1 (never or very rarely true) to 5 (very often or always true). Higher scores indicate a greater capacity for mindfulness. The internal consistency of this assessment tool is 0.86.

*Self-Compassion Scale* short form (SCS-SF) [52] consists of 12 items assessing 6 factors: Self-Kindness, Self-Judgment, Common Humanity, Isolation, Mindfulness, and Over-identification. Each item can be rated on a Likert-type scale from 1 (almost never) to 5 (almost always). Higher scores indicate greater self-compassion. The internal consistency of this instrument is 0.85.

*Satisfaction with Life Scale* (SLS) [53] consists of 5 items with a 7-point Likert-type scale (from 1, strongly disagree; to 7, strongly agree). The score ranges from 5 to 35, with higher scores indicating greater satisfaction. The internal consistency of this instrument is 0.88.

*Marlowe-Crowne Social Desirability Scale* short form (M-C SDS Scale) [54] consists of 18 items, 13 items reflecting very frequent undesirable behaviours and traits, and other 5 items reflecting infrequent socially desirable behaviours and traits. The person being assessed must indicate whether they are true or false with regard to him/herself. The sum of the scores gives a total score between 0 and 18, where a higher score indicates a higher social desirability, understood as a response bias or personality trait. It internal consistency is 0.76.

*Mediterranean Diet Adherence Test* [55] is a brief dietary assessment consisting of 14 questions that evaluates adherence to the Mediterranean Diet pattern. This questionnaire scores one point per question, with a score of <9 meaning low adherence and a score of > = 9 meaning good adherence.

*Insomnia Severity Index* (ISI) [56] is a 5-item self-report instrument that assesses the severity of the sleep problem, the degree of dissatisfaction and the impact on quality of life. Scores range from 0 (best score) to 28 (worst score). The internal consistency of this instrument is 0.82.

*International Physical Activity Questionnaire* short form (IPAQ-SF) [57] is a self-administered questionnaire consisting of 7 items that assesses the time spent being physically active in the last 7 days. The internal consistency of this assessment tool is 0.337.

*Plymouth Sensory Imagery Questionnaire* (Psi-Q) [58] measures vividness of mental imagery and consists of 21 items measuring 7 sensory modalities: vision, sound, smell, taste, touch, bodily sensation and emotions. The questionnaire has a Likert-type scale between 1 (no imagery) and 7 (perfectly clear and as vivid as the actual experience). The internal consistency of this instrument is 0.88.

*Intervention adherence*. During weeks 1–6 of MBHC program, adherence will be recorded by means of: 1) class attendance, 2) number of minutes practicing mindfulness each day (question number 11 of the EMA). In the follow-up period (weeks 7–18) participants will receive a weekly survey asking for the frequency (number of days per week) and duration of mindfulness practice (minutes) during the last week [59].

*Ecological momentary assessment*. This evaluation "at the moment" and "in the current context" presents multiple methodological advantages compared to traditional data collection systems: 1) it reduces memory bias by obtaining current or recent experience information; 2) allows the collection of information in the environment of the subject, increasing compliance and reliability; 3) and allows the detection of variations over time and factors that influence the evolution of the participants [34]. Our EMA will include 11 questions (Table 2) assessing occupation (question 1), volition (question 2), mindfulness state (question 3), well-being state (questions 4 and 9), positive and negative affect of high and low arousal (questions 5 and 6), state stress (question 7), self-compassion (question 8), recovery experience (question 10) and monitoring of daily mindfulness practice (question 11). Questions 2 to 11 will be answered using a visual analogue scale from 0 to 10 points.

**Table 2 pone.0302018.t002:** Questions included on Ecological Momentary Assessment (EMA).

1. What are you doing right now?
2. This activity is motivating for me
3. I was thinking about something other than what I was doing right now
4. What is my mood right now?
5. I have felt happy and in a good mood while doing that activity
6. I have felt calm and relaxed while doing that activity
7. What is my stress level right now?
8. While doing the activity, have I given to myself the care and kindness that I need?
9. What is my level of happiness right now?
10. In the last 24 hours I have carried out some recovery activity/experience (I have slept well, I have played sports, leisure activities, etc.)
11. In the last 24 hours, how many minutes have I spent practicing mindfulness?

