### Hypotheses

We hypothesized that, compared to the waiting list control group, both MBHC and MBHC-VR will improve occupational indicators (Hypothesis 1), mental health (Hypothesis 2), and psychological functioning (Hypothesis 3). We expect that, compared to MBHC, MBHC-VR will have higher adherence to home practice [5], and result in greater magnitude of change in the occupational balance, mental health and psychological functioning variables (Hypothesis 4). Furthermore, we expect that improvements will be maintained at 3-months post-intervention completion [5] (Hypothesis 5). Finally, we predict that psychological functioning variables will act as mechanisms of change of occupational balance and mental health indicators in experimental vs control condition [35] (Hypothesis 6). All hypotheses will be tested in the post-training assessment, except for hypothesis 5, which will be tested in the follow-up.

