In this study, special attention is also paid to the possibility of adverse effects associated with the practice of meditation, as evidenced by previous studies [64, 88, 89]. In anticipation of this, the participants will communicate to the research team any difficulty or symptomatology that may arise, in order to attend to and solve these events as quickly as possible and, if necessary, refer the participant to the specialized psychological services available at the university. Likewise, participants will also report possible adverse effects during and/or after VR exposure. In the MBHC-VR group of this research, VR with neutral and pleasant contents will be used in all sessions for a time between 10 and 15 minutes, favoring adaptation to the exposure and minimizing possible adverse effects.

It is also worth mentioning that the programs will be implemented by a multidisciplinary professional group with extensive experience in university education and highly qualified in MBIs. In this sense, the team is made up of occupational therapists, psychologists, physiotherapists, mindfulness experts and university professors’ experts in teaching and research.

In terms of feasibility, face-to-face interventions will be carried out in groups of about 15 people, who can be attended simultaneously, thus being a low-cost community mindfulness program for university students. If the MBHC programs designed for this study are effective, one of the advantages is that their applicability can be extended to other universities. Also, the materials and procedures will be available to the educational and scientific community. Thus, the range of effective interventions available to address university students’ mental health will be expanded.

The present trial can also contribute to expanding knowledge on personalized treatments. Baseline characteristics of individuals have started to be used as predictive factors of differential response to intervention strategies. This study will allow identifying individuals within the included sample that will benefit more from utilizing one condition relative to the other. It will also allow to establish moderating mechanisms of efficacy.

In short, and from the point of view of clinical practice, it is expected that with the proposed intervention university students will learn to relate in a healthier way with their mental processes, so as to improve their OB and their psychological well-being.

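### EMA question 11, the only weeks 1–6 measure of home practice, asks for minutes but is answered on an unanchored 0–10 scale; two constructs listed as EMA-measured have no EMA item

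*Protocol article*

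**What the plan says.** All references are to the protocol article.

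- **Intervention adherence.** In weeks 1–6, adherence is class attendance plus the "number of minutes practicing mindfulness each day (question number 11 of the EMA"). In weeks 7–18 it comes from a weekly survey of the number of practice days and the "duration of mindfulness practice (minutes) during the last week".
- **Table 2, question 11.** The item reads "In the last 24 hours, how many minutes have I spent practicing mindfulness".
- **Ecological momentary assessment.** "Questions 2 to 11 will be answered using a visual analogue scale from 0 to 10 points". The same paragraph assigns each of the 11 items to a construct.
- **Hypotheses.** Hypothesis 4 predicts that "compared to MBHC, MBHC-VR will have higher adherence to home practice". Every hypothesis except the fifth is tested at the post-training assessment.
- **Measures.** During the six programme weeks, "information about perceived stress, emotional regulation, mindfulness, self-compassion, psychological flexibility, and volition will be collected daily" through the EMA.
- **Table 1.** Emotional dysregulation and psychological flexibility each carry an inter-session cross, and EMA is named as a method beside DERS and AAQ-II respectively.

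**The concern.** The adherence paragraph and Table 2 need a count of minutes. The response format assigned to the same item is a 0–10 scale, which is not a count of minutes unless one point happens to be one minute, and in that case it stops at 10. Better adherence is a main reason the article gives for adding VR, and the first clause of Hypothesis 4 depends on it. Attendance says nothing about practice at home, so question 11 carries that clause alone in weeks 1–6. Daily responses stored on the wrong scale cannot be repaired afterwards.

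The second mismatch is smaller. Two constructs are announced as having daily in-programme values, but the printed instrument has nothing assigned to produce them.

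**Working it through.** **Question 11.** The plan states no figure to reproduce, so the check is whether the passages fit together.

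1. Quantity required: minutes per day (Intervention adherence; Table 2).
2. Response recorded: 0 to 10 on a visual analogue scale (Ecological momentary assessment). No end labels and no minutes-per-point rule are given.
3. Possible rescue: the Measures section says the form mixes text and visual analogue items. The scale sentence covers questions 2 to 11, so only question 1, on current activity, is left as a text item. Question 11 is not exempted.
4. Two readings remain:
   - One point is one minute. Then recorded = min(true minutes, 10), and all days at or above 10 minutes look alike.
   - The scale is a rating. Then there is no mapping back to minutes, and the measure defined in the adherence paragraph does not exist.

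**Illustration of the first reading only.** The documents give no mean or SD for daily practice, so every mean and SD below is an assumption, as is one point per minute. Daily minutes were drawn from gamma distributions (2,000,000 draws per arm) and capped at 10. The true d is the mean difference divided by the SD. The recorded d is the capped mean difference divided by the square root of the average of the two capped variances.

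| Assumed means (SD) | True difference | Recorded difference | Retained | Days at cap, by arm | d, true → recorded |
|---|---|---|---|---|---|
| 5 vs 8 (5) | 3 | 2.44 | 2.44/3 = 81% | 14%, 28% | 0.60 → 0.79 |
| 10 vs 13 (8) | 3 | 1.45 | 1.45/3 = 48% | 39%, 58% | 0.38 → 0.51 |
| 12 vs 15 (8) | 3 | 1.08 | 1.08/3 = 36% | 52%, 70% | 0.38 → 0.47 |
| 15 vs 20 (8) | 5 | 0.77 | 0.77/5 = 15% | 70%, 92% | 0.62 → 0.56 |
| 20 vs 25 (10) | 5 | 0.32 | 0.32/5 = 6% | 86%, 97% | 0.50 → 0.36 |

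The difference in minutes shrinks in every row, by very different amounts. The standardised difference rises in three rows and falls in two, because capping also removes the upper tail and so reduces the SD. The illustration therefore supports a distorted estimate in minutes but not a general loss of power.

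**EMA constructs against items.** Table 1 names EMA for seven constructs. Under the item map:

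- stress: question 7
- mindfulness: question 3
- self-compassion: question 8
- volition: question 2
- adherence: question 11
- emotional dysregulation: none
- psychological flexibility: none

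The remaining items are occupation (1), well-being (4 and 9), affect (5 and 6) and recovery (10). The article labels questions 5 and 6 as affect and does not present them as emotion regulation. Five of the seven constructs have an item and two do not.

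**The case against.** The strongest reply is that this is a drafting slip. Two places say minutes, and only the blanket range of question numbers conflicts, so an 11 typed for a 10 is quite plausible. That is fair, and the point is best classed as an internal contradiction and not as a deliberate design choice. The printed plan still has to be corrected, because a form built from it would not yield minutes.

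A reader might infer four stronger things, and the documents support none of them.

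- **That practice of 10 minutes or more certainly cannot be told apart.** This needs one point to equal one minute, which the article never says.
- **That one VR practice at home already reaches the top of the scale.** The Discussion says VR "will be used in all sessions for a time between 10 and 15 minutes". That describes sessions. No length is given there for home practice or for the MBHC arm.
- **That a ceiling hides the adherence effect, or that the two adherence periods are made incomparable.** The illustration shows shrinkage in raw minutes with the standardised difference moving either way. The two periods use different instruments anyway, and the article plans no comparison between them.
- **That Hypothesis 6 loses two mediators.** It is tested at post-training, where DERS and AAQ-II are both collected, and the structural equation section does not say that EMA values enter the model.

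**Conclusion.** The contradiction over question 11 stands. Followed as written, the plan would not give usable practice minutes for weeks 1–6: either values above 10 minutes are truncated, or a rating is stored that cannot be converted. The between-arm difference in minutes is distorted in both cases. The documents do not fix the amount. Under the assumed inputs and one point per minute, the retained share of the true difference ranged from 81% down to 6%, which shows only how strongly the answer depends on unknown practice levels. Class attendance and the weeks 7–18 survey are unaffected.

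The second mismatch also stands, as two EMA entries with no item behind them. Its reach is limited to the inter-session values of emotional regulation and psychological flexibility; the questionnaire measures at pre, post and follow-up are intact. Neither point touches the sample size.

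**What to change.** 1. Make question 11 a free numeric entry in minutes, with 0 allowed, and change the scale sentence so that the 0–10 visual analogue scale applies to questions 2–10. This is one field in an online form and one corrected sentence. If the live form already takes a number, only the sentence needs correcting.
2. For emotional regulation and psychological flexibility, either add one EMA item for each and enter it in the item map and Table 2, or delete their inter-session crosses and EMA entries in Table 1 and their EMA mentions in Measures. The first option costs two short daily items; the second costs only text edits.
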